### Outcome measures

All assessments will be conducted at baseline, endpoint (8 weeks after treatment commencement), and follow-up (8 weeks and 24 weeks after the end of treatment). All questionnaires are in Chinese [17].

#### Primary outcome measure

The primary outcome measure includes changes of MoCA score. The MoCA test is a special tool to assess eight cognitive domains, including short-term memory recall, visuospatial abilities, language, attention, working memory, orientation to time and place, concentration as well as executive functions, among which the last two are the most notable aspects for VCIND. Executive functions are assessed by the alternating trail making task, verbal fluency task and the two-item verbal abstraction task; while concentration is evaluated by a sustained attention task, a serial subtraction task and digits forward and backward task. A final score ≥ 26 usually indicates normal cognitive ability, while a score below that level indicates cognitive impairment. This test will be administrated in approximately 10 minutes.

#### Secondary outcome measures

The ability of daily life will be evaluated by using the MBI. It involves 10 variables and a higher score indicates a greater likelihood of being able to live at home independently [18].

ERP provides a non-invasive way to evaluate brain function in patients with cognitive impairment by observing the typical electrophysiological response to a stimulus. In this RCT, it is the P300 component abnormalities (change of latent period and wave amplitude) that will be observed [19].

### Blinding

Except for the acupuncturists, patients and researchers who measure the outcomes will be blinded to the randomization in this RCT.

### Safety assessment

All participants are asked to report any adverse event related to the treatment they are undergoing to the specific researcher in charge of assessing adverse effects. The details of every adverse event, including following management and final outcome, will be reported in the Case Report Form.

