**Discussion:**

If the outcome confirms the effectiveness and safety of electrical acupuncture in treating VCIND, this treatment is expected to be promoted in clinical practice to treat such patients.

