#### Inclusion criteria

Patients aged 45–80 years who (1) complain of or are reported by a relative or accompanying person as having cognitive decline; (2) have imaging evidence that supports cerebrovascular disease, and may or may not have a medical history of transient ischemic attack or other types of stroke; (3) have symptoms or signs caused by cerebrovascular disease (e.g., hemiplegia, hemiparesis, problems with understanding or forming speech, numbness or strange sensations); and (4) obtain the following results in the neuropsychological assessment under professional instruction from the neurologist: MoCA score < 26; clinical dementia rating scale score = 0.5; modified Rankin scale score ≤ 3; Hachinski ischemic score > 7 points, will be included in the study.

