#### Exclusion criteria

Patients who (1) have a Mini-mental State Examination score < 21; (2) have co-morbidity including AD, Parkinson’s disease, frontotemporal dementia, or Huntington’s disease, central nervous system inflammatory demyelinating disease, epilepsy, psychosis, liver or kidney dysfunction, hypothyroidism, alcoholic or drug abuse related encephalopathy, depression; and (3) have severe visual impairment, hearing impairment, severe aphasia or limb dysfunction which might affect pre-assessment, will be excluded from the study.

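### The stated rule asks patients to report treatment-related adverse events, so the patient's own view of causality filters harms before anyone assesses them, and under-counting is likely

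*Protocol article*

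**What the plan says.** The protocol article deals with the collection of harms in one short section, Safety assessment. It states: "All participants are asked to report any adverse event related to the treatment they are undergoing". Reports go "to the specific researcher in charge of assessing adverse effects". The section then adds: "The details of every adverse event, including following management and final outcome, will be reported in the Case Report Form".

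Three other places bear on how this rule will work:

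- **Inclusion criteria.** Entry requires "MoCA score < 26; clinical dementia rating scale score = 0.5", so reporters are selected for cognitive impairment. They also have symptoms or signs of cerebrovascular disease, which may include speech problems.
- **Exclusion criteria.** Patients who "have a Mini-mental State Examination score < 21" are excluded, as are those with severe aphasia. The impairment is therefore mild.
- **Abstract, Discussion.** Promotion of the treatment in practice is tied to a condition that includes safety: "If the outcome confirms the effectiveness and safety of electrical acupuncture in treating VCIND".

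**The concern.** The usual order is to collect every untoward event first and judge its cause afterwards. The rule as written reverses this: the request to the patient already contains the causality judgement, so the researcher appointed to assess adverse effects sees what has passed that filter.

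This matters more here than in many trials. Dizziness, a fall or a new vascular event has an obvious alternative explanation in a patient with cerebrovascular disease. A patient asked about effects of the treatment may reasonably leave it out. Cognitive impairment, even mild, and possible speech difficulty make unprompted reporting less dependable. The Inclusion criteria accept a relative's or companion's account of cognitive decline, but the Safety assessment section names the participant alone as the source of harms.

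At stake is the meaning of a low adverse-event count. A clean record could reflect a safe treatment or a narrow question, and the data could not tell the two apart.

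**Working it through.** **Step 1: set the sentences of the Safety assessment section side by side.**

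- The first sentence defines what reaches the researcher: events that the participant regards as related to treatment.
- The second sentence defines what is documented: every adverse event, with no relatedness limit.
- No other route by which an event could arrive is stated in the article.

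The two sentences differ in scope. Read together, the second can be guaranteed only for events that have passed the first. The likely direction of error is under-counting.

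**Step 2: is there a figure to reproduce?** No. The article gives no adverse-event rate, reporting share or safety sample size. What follows is an illustration on assumed reporting shares.

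**Step 3: inputs.**

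- n = 60 per arm (Abstract, and the sample-size text under Dropout criteria).
- s = share of patients with an event whose event is reported. Assumed values are 1.0, 0.7, 0.5 and 0.3.
- p = true proportion of patients with an event.

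Patients are treated as independent, and all 60 are assumed to be observed.

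**Step 4: upper bound when nothing is reported.** The chance of zero reports is (1 − p·s)^60. Setting this to 0.05 gives

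p_upper = (1 − 0.05^(1/60)) / s = 0.0487 / s

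| Share reported, s | Calculation | One-sided 95% upper bound on p |
|---|---|---|
| 1.0 | 0.0487 / 1.0 | 4.9% |
| 0.7 | 0.0487 / 0.7 | 7.0% |
| 0.5 | 0.0487 / 0.5 | 9.7% |
| 0.3 | 0.0487 / 0.3 | 16.2% |

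The 4.9% in the first row comes from the sample size alone and would hold under perfect collection. Only the rise above 4.9% illustrates the effect of the collection rule.

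**Step 5: chance of seeing at least one report in an arm, 1 − (1 − p·s)^60.**

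| True rate p | s = 1.0 | s = 0.7 | s = 0.5 | s = 0.3 |
|---|---|---|---|---|
| 2% | 70% | 57% | 45% | 30% |
| 5% | 95% | 88% | 78% | 60% |

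An event type affecting 1 patient in 20 would almost certainly appear under full reporting. It would be missed altogether in about 4 of 10 such arms if 30% of events were passed on.

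**The case against.** **The documentation sentence has no relatedness limit.** It promises every event, and the article does not say that patient report is the only source. This has weight: it would be wrong to say that unattributed events can never reach the Case Report Form. What can be said is that the article states no route for them. At the least, the two sentences need to be reconciled.

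**Routine enquiry may be described elsewhere.** The Design section refers to Fig. 2 and Additional file 1 for data collection, and neither is at hand. Visit-by-visit questioning, causality grading and adverse-event tables are often left to such documents, and their absence here is not a fault. The point rests on the rule that the article does state. If a fuller document asks about all events, this sentence misdescribes it and should still be corrected.

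**The patients are only mildly impaired.** The Mini-mental State Examination limit, the exclusion of severe aphasia and three sessions a week all help reporting. This stands, and it moderates the concern. It does not remove it, because the filter is in the request itself and would act in patients with intact cognition too.

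**A reader might infer that under-reporting will differ between arms.** The arms do differ in insertion and current, and Table 1 lists the control arm as lacking de-qi. However, the Blinding section states: "Except for the acupuncturists, patients and researchers who measure the outcomes will be blinded to the randomization in this RCT". Patients in both arms have a visual barrier, have it implied that what they feel is real acupuncture, and, according to the sham description, have a similar sensation. A difference by arm is possible, but the document does not show one.

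**Safety is not a formal aim.** Neither the Hypothesis nor the Objectives mentions it, and no between-arm comparison of harms is set out. The safety claim is one conditional sentence in the abstract. That limits the consequence, but the sentence still makes promotion of the treatment depend in part on safety.

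**Conclusion.** The point holds in a limited form. The reporting rule places the patient's view of causality ahead of the researcher's assessment, and the promise to document every event names no source that bypasses it. Harms are therefore likely to be under-counted.

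The amount cannot be derived from the document. With no reports among 60 patients, the upper bound would move from 4.9% under full capture to between 7.0% and 16.2% if 70% down to 30% of events were reported. Those shares are assumptions and are not estimates for this trial.

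Two stronger readings are not supported: that events not attributed to needling are certain to be lost, and that the arms will be affected unequally. The primary outcome and its analysis are untouched. The change is worth making because events not asked about at the time cannot be reliably recovered later.

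**What to change.** 1. In the Safety assessment section, delete the words that limit reports to treatment-related events, so that the request matches the promise to document every event.
2. At existing visits or follow-up contacts, ask the patient and, where present, the companion one fixed, scripted open question about any new or worsened symptom, worded identically in both arms.
3. State who asks. The acupuncturists are present at every session but are not blinded, so the question is better put by the adverse-effects researcher or an outcome assessor. The Blinding section covers those who measure outcomes and does not expressly name the adverse-effects researcher, so add that this person is kept unaware of arm.
4. Record all adverse events regardless of presumed relation. Have the designated researcher judge causality afterwards, without knowledge of arm.
5. Report the number of patients with any event by arm with 95% confidence intervals, and limit the safety conclusion to what 60 per arm can exclude.

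**Cost.** No new visits are needed. The workload depends on the contacts chosen: asking at the three post-baseline assessments is 3 × 120 = 360 enquiries, and asking at every session is 24 × 120 = 2,880. Fewer contacts mean longer recall, which is a drawback in this population. More frequent asking by someone other than the acupuncturist may take additional staff time. More unrelated events will also be recorded and will need assessment.

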### Monitoring

The entire process of this RCT will be conducted under the supervision of a qualified clinical trial expert, and all original data of the RCT will be inputted into and stored on the ResMan research Manager of the Clinical Trial Management Public Platform. The Clinical Research Center of Drugs of the Shanghai University of Traditional Chinese Medicine takes charge of data monitoring, i.e., having access to any interim results and making the final decision to terminate the trial.

### Data analysis

All original data will be entered and stored with Microsoft Excel 2010, while data from cases without baseline evaluation or follow-up will be excluded from the full analysis set, and analyses will be performed with SPSS version 23.0 software. In the statistical analysis, measurement data will be analyzed with the Student’s *t* test, ranked data with the rank sum test, and categorical data with χ^2^ test. Data will be expressed as mean ± standard deviation or median (first quartile, third quartile). All reported *P* values will be two-sided with confidence intervals at the 95% level, and a *P* value of less than 0.05 will be considered statistically significant.

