#### Dropout criteria

Patients who (1) have poor clinical compliance (2) quit the RCT voluntarily will be considered as having dropped out.

In this procedure, we used the formula for calculating the sample size of two sample rates for disordered classified data. Taking the results of previous research with a similar study design of acupuncture arm [15] (RR = 80%, OR = 15%) into consideration, a sample size of 100 patients (50 for each group) should be recruited. Allowing 20% attrition, the recruited sample size for this RCT will be of 120 patients (60 in each group).

Upon fulfillment of selection criteria, 120 eligible participants will be randomly allocated into the intervention and control groups in a 1:1 allocation ratio. Randomization will be performed according to a random list of numbers generated by the randomization center of Shanghai University of Traditional Chinese Medicine. An independent researcher, who contacts no participant and is not involved in the data collection or analysis, will take charge of the participant allocation based on the mentioned random list as well as on the allocation sequence concealment.

All participants will receive moderate financial subsidies to cover the travel expenses and should stick to the schedule for all treatments and assessments as much as possible. Those who are unable to visit the clinic at the time of reservation should inform the instructor by phone in advance to reschedule.

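### The full analysis set drops randomised patients who lack an undefined follow-up, leaving the primary MoCA comparison open to attrition bias of unknown size and direction

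*Protocol article*

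**What the plan says.** The protocol article fixes the analysis set in its Data analysis section: "data from cases without baseline evaluation or follow-up will be excluded from the full analysis set". It names no other set. The same section states that "measurement data will be analyzed with the Student’s *t* test", a test that uses observed values only. The primary endpoint is given thus: "The primary outcome measure includes changes of MoCA score".

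Outcome measures lists the post-baseline assessments as "endpoint (8 weeks after treatment commencement), and follow-up (8 weeks and 24 weeks after the end of treatment". The Abstract makes the same split between endpoint and follow-up.

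Under Dropout criteria: "Patients who (1) have poor clinical compliance (2) quit the RCT voluntarily will be considered as having dropped out". No threshold for poor compliance is given, and the text does not say what happens to these patients' assessments or data. The same section states "a sample size of 100 patients (50 for each group) should be recruited", and then "Allowing 20% attrition, the recruited sample size for this RCT will be of 120 patients (60 in each group". Patients are "randomly allocated into the intervention and control groups in a 1:1 allocation ratio".

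**The concern.** Randomisation makes the two arms comparable as allocated. A rule that keeps a patient only if a later visit took place conditions the comparison on something that happens after allocation and that treatment may influence. The arms differ in what patients undergo (insertion, needle manipulation and current in one; a blunt needle with the device off in the other), so different reasons for leaving are plausible, though not shown.

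The wording adds a second problem. Follow-up has a specific meaning in Outcome measures that excludes the week-8 endpoint. Under that meaning the rule discards week-8 MoCA scores that were actually collected. Under a broader meaning it does not. Nothing in the article settles which applies, so the choice could be made after the data are seen.

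At stake are the effect estimate and P value for MoCA. Both can be wrong if the patients removed differ in prognosis between arms.

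**Working it through.** **1. The plan's own attrition figure.** Inputs are from Dropout criteria: 100 evaluable, 20% attrition, 120 recruited. 100 × 1.20 = 120, which reproduces the stated total. Losing 20% of 120 removes 24 patients and leaves 96 (48 per arm if the loss is equal). The plan therefore expects this rule to act on about 24 patients.

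**2. Who is removed under each reading.**

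| Patient | Follow-up = visits 8 and 24 weeks after treatment | Follow-up = any post-baseline visit |
|---|---|---|
| Baseline and week-8 MoCA, no later visit | Removed | Kept |
| Lost before week 8, never seen again | Removed | Removed |
| Poor complier who attends the visits | Not removed by this rule | Not removed by this rule |

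**3. Illustrative size; the dropout pattern is assumed, not taken from the plan.** The true effect is zero, with 60 per arm and the outcome in SD units. The outcome has correlation r with a latent tendency to drop out, and the lowest fraction q of each arm on that tendency is lost. The mean of those retained is r·λ(q), where λ(q) = φ(z_q)/(1 − q) and z_q is the q-quantile of the standard normal. Bias = r·[λ(q₁) − λ(q₂)].

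- 30% against 10%: λ = 0.497 and 0.195. With r = 0.5, bias = 0.5 × 0.302 = 0.15 SD.
- The retained outcome variance is 1 − r²(λ² − z_q·λ), which gives 0.873 and 0.928. With 42 and 54 patients, SE = √(0.873/42 + 0.928/54) = 0.195.
- Type I error = Φ(−1.96 + 0.151/0.195) + Φ(−1.96 − 0.151/0.195) = 12.1%. A simulation of 20,000 trials gave 11.8%.

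The biases below follow from the formula; the type I errors are from the simulation.

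| Loss by arm | r | Bias (SD) | Type I error |
|---|---|---|---|
| 30% / 10% | 0.3 | 0.09 | 7.2% |
| 30% / 10% | 0.5 | 0.15 | 11.8% |
| 30% / 10% | 0.7 | 0.21 | 20.3% |
| 25% / 15% | 0.5 | 0.07 | 6.5% |
| 20% / 20%, same mechanism | any | 0 | about 5% |

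Swapping the arms reverses the sign of the bias and leaves its size unchanged.

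**4. Equal loss is not a complete safeguard.** Suppose 20% leave each arm, but in one arm only those lost are g SD worse than those retained. Bias = 0.20·g. For g = 0.5 it is 0.10 SD; with SE = √(2/48) = 0.204, type I error is 7.8%.

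**5. Scale.** With 48 per arm and an assumed 80% power (the article states none), the detectable difference is (1.96 + 0.84) × √(2/48) = 0.57 SD. A bias of 0.15 SD is about a quarter of that.

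**6. What a missing-at-random model would recover.** Take the 30%/10%, r = 0.5 case and adjust for a baseline correlated 0.5 or 0.7 with outcome and linked to dropout only through outcome (6,000 simulated trials each). Bias falls from about 0.15 to about 0.11–0.12 or 0.08 SD. Type I error falls to roughly 10–11% or 9%. Adjustment helps but does not remove the bias.

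**The case against.** The strongest reply is that the rule may be milder than it looks. Paired with baseline evaluation, follow-up can naturally mean any later assessment, and the Discussion uses the word loosely for phone or home contact. The set would then be a modified intention-to-treat set. This stands: a reader might infer that the plan commits to a completer analysis, but that depends on the narrow reading and is not established. It does not rescue the rule, because patients lost before the endpoint are removed on either reading.

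A reader might also infer that poor compliers are removed from the analysis, or that the unblinded acupuncturists decide who they are. The article says neither. The exclusion rule does not mention compliance, and no section says who judges it. What remains is an omission that matters: the label dropout is applied without saying whether assessment continues.

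The 12% and 20% error rates could be read as the expected cost of the rule. They are not. The plan suggests no imbalance in loss. Patient blinding, a placebo needle, identical schedules, subsidies and rescheduling all work against one. Part of that bias would also survive the recommended model.

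Finally, imputation and sensitivity analyses are usually left to an SAP, and their absence here is not the complaint. The exclusion rule is stated in the article itself.

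**Conclusion.** The concern holds in this limited form. The article states a rule that removes randomised patients from its only named analysis set on the basis of later attendance, using a term whose literal meaning there would discard observed week-8 MoCA scores. The handling of poor compliers is unclear rather than wrong.

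The resulting bias has unknown size and direction. Under the assumed patterns above with r = 0.5 it ranges from none (equal loss, same mechanism) through about 0.07 SD (25%/15%) to about 0.15 SD (30%/10%). These figures rest on assumed loss rates, an assumed link between dropout and outcome, and a true effect of zero. They show what the rule permits, not what will happen. Because the rule governs the primary comparison, and assessments not made cannot be recovered later, the wording should be settled before patients are lost.

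**What to change.** - Define the full analysis set as all randomised patients, analysed in their assigned arm.
- Include every patient with a week-8 MoCA in the week-8 comparison, whether or not later visits took place.
- State that poor compliance or stopping treatment neither ends the scheduled MoCA, MBI and P300 assessments nor removes the patient from the analysis. The home-visit and phone follow-up foreseen in the Discussion can support this.
- Analyse MoCA with a baseline-adjusted mixed model over all available visits, or with multiple imputation. Say plainly that this assumes missing at random and would remove only part of any outcome-dependent bias.
- Report the currently worded set as a sensitivity analysis, with follow-up defined, and add one delta-adjusted analysis.

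The cost is revised wording, a little more analysis work (the mixed model can be run in the SPSS version already named) and continued visits for patients who stop treatment. No additional patients are needed.

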## Discussion

In the past few years, acupuncture therapy has been used in clinical practice on VCIND for relieving symptoms and delaying progression. However, the existing literature regarding those practices are basically empirical and with inevitable deficits such as small sample size or short duration [20]. In this trial, we used the study by Lao et al. [21], which reported the successful implementation of sham acupuncture, as a reference and will perform the control-group intervention, namely sham acupuncture, to rule out the placebo effect of acupuncture in a very rigorous way. By designing this RCT – with an improved design and methods – we aim to contribute better evidence for the effectiveness of electrical acupuncture, which is expected to reduce the extent of damage to nerve cells in the hippocampus, leading to a neuro-protective effect [22] in vascular cognitive impairment.

The second improvement we make in this study is the selection of participants. Symptoms like mild functional impairment for complex tasks can typically be apparent in mild cognitive impairment, early single dementia, or even multiple etiology dementias [23]. Thus, it is clinically difficult to identify patients with pure VCIND, and results based on that population might not be generalizable to clinical practice. To avoid this problem, we chose to target early cognitive impairment populations or pre-VCIND populations, rather than those clearly diagnosed as vascular cognitive impairment.

Finally, to promote good patient compliance, we will try to facilitate each step of the trial, including the appointment process, treatment conduction, and phone call or home visiting follow-up, as well as offering moderate financial subsidies.

